## 7 Objectives

### 7.1 Primary objective

1. Stage 1 : To find out the optimal biological and clinically effective metronomic dose (OBD) of methotrexate when given in combination with celecoxib and erlotinib
2. Stage 2 : To find out the median PFS (Progression free survival) in recurrent oral cancer patients with the combination of celecoxib, erlotinib and methotrexate in OBD

### 7.2 Secondary objective ( both stages)

1. To find out the frequency of maximum grade of toxicity (hematological and non hematological) in accordance with CTCAE (common terminology criteria for adverse events, NCI,USA) version 4.03 with the combination metronomic therapy
2. To study the evolution in serum and tissue biomarker levels during metronomic chemotherapy and their relationship to disease control
  - a. Serum angiogenic biomarkers : VEGF, VEGFR1-3, Tie-2, Angiopoietin 1-2, Thrombospondin 1, Vaso-inhibin, Angiostatin, Endostatin ,IL-8, Circulating endothelial cells and Endothelial progenitor cells,CAIX,osteopontin,
  - b. Tumor tissue marker : Thymidine phosphorylase, Hypoxia inducible factor I-alpha, DLL, SPARC , FOX-p3 Treg
3. To develop Pharmacokinetics-Pharmacodynamics (PK-PD) Model of methotrexate using CECs and serum angiogenic biomarkers as PD endpoints

### 7.3 Tertiary objective (both stages)

To study gene expression changes in the tumor tissue during MCT-E to identify responders and mechanisms of resistance.

1. To analyze HPV, markers of inflammation, cell proliferation, apoptosis and hypoxia to evaluate the association with treatment response.
2. To identify the transcriptomic alterations and to delineate the genes/gene clusters which are differentially regulated in response to the treatment.
3. To carry out global miRNA profiling in tissue and serum samples to identify miRNAs differentially regulated in response to the treatment.

## 8 Study Design

Non randomized open label stage I using novel de-escalation schema would be followed by non randomized open label stage II

## 9 Study Setting

Patients will be recruited at Tata Memorial Hospital / ACTREC which is a tertiary cancer centre located in Mumbai , India

## 10 Eligibility Criteria

### 10.1 Inclusion Criteria

1. Participants must have histologically confirmed squamous cell cancers of the oral cavity warranting palliative chemotherapy.
2. Patients should have failed within 1 month of surgery/ radiation or within 6 months of platinum based systemic therapy who couldn't afford cetuximab we offer metronomic chemotherapy at present.
3. Participants must have measurable disease, defined as at least one lesion that can be accurately measured in at least one dimension (longest diameter to be recorded for non-nodal lesions and short axis for nodal lesions) as  $\geq 20$  mm with conventional techniques or as  $\geq 10$  mm with spiral CT scan, MRI, or calipers by clinical exam.

4. Age : Any age above 18 years. No maximum age.
5. ECOG performance status  $\leq 2$
6. Life expectancy of less than 6 months with standard palliative treatments.
7. Participants must have normal organ and marrow function as defined below:
  - a. Leukocytes  $\geq 3,000/\text{mcl}$
  - b. Platelets  $\geq 100,000/\text{mcl}$
  - c. Total bilirubin  $< 1.5 \times$  institutional upper limit of normal
  - d. AST(SGOT)/ALT(SGPT)  $\leq 2.5 \times$  institutional upper limit of normal
  - e. Calculated Creatinine clearance  $> 30 \text{ ml/min}$
8. The effects of erlotinib , oral methotrexate and celecoxib on the developing human fetus are unknown. For this reason and because all these agents used in this trial are known to be independently teratogenic, women of childbearing potential and men must agree to use adequate contraception (hormonal or barrier method of birth control; abstinence) prior to study entry and for the duration of study participation. Should a woman become pregnant or suspect she is pregnant while she or her partner is participating in this study, she should inform her treating physician immediately. Men treated or enrolled on this protocol must also agree to use adequate contraception prior to the study, for the duration of study participation, and 6 months after completion of protocol.
9. Both men and women of all races and ethnic groups are eligible for this trial.
10. Ability to understand and the willingness to sign a written informed consent document

## 10.2 Exclusion Criteria

1. Participants who are receiving any other investigational agents.
2. Patients with history of aspiration pneumonia or who are unable to swallow tablets
3. Primary sites of malignancy in major salivary gland or nasopharynx or skin
4. Patients receiving methotrexate for other indications not limited to rheumatoid arthritis
5. Patients who had received long term Cox-2 inhibitors ( more than 3 month continuous usage) will be excluded
6. Patients with hypercalcemia at presentation (defined as a corrected serum calcium of  $> 10.5 \text{ mg/dL}$ ).

7. Patients with QTc prolongation defined as QTc interval greater than 440 ms in males and 480 ms in females in view of risk of sudden cardiac death associated with use of celecoxib.
8. History of allergic reactions attributed to compounds of similar chemical or biologic composition to any agents used in study.
9. Uncontrolled intercurrent illness including, but not limited to, hypertension, tuberculosis, diabetes, ongoing or active infection, symptomatic congestive heart failure, unstable angina pectoris, cardiac arrhythmia, renal failure (on dialysis), active gastrointestinal bleeding, cerebrovascular accidents, inflammatory bowel disease, known hyperkalemia (CTCAE version 4.02 grade 3 or above which is persistent over 1 week) or psychiatric illness/social situations that would limit compliance with study requirements.
10. Pregnant women and breastfeeding women are excluded from this study because celecoxib / erlotinib and methotrexate are agents with the potential for teratogenic or abortifacient effects. Because there is an unknown but potential risk for adverse events in nursing infants. These potential risks may also apply to other agents used in this study.
11. HIV-positive, Hepatitis B and C seropositive patients are excluded from this study.
12. Patients with previous history of other cancers.

## 11 Interventions

### 11.1 Prerequisite for administration of metronomic therapy

Patients meeting the inclusion criteria who give written informed consent will be started on metronomic chemotherapy (MCT) with erlotinib, celecoxib and oral methotrexate. Patients on MCT would be monitored for response (RECIST version 1.1) and toxicity (CTCAE version 4.03) at C1D8, D30 and subsequently monthly till progression. Response at 2 months will be considered for stage 1 study decisions on selection of dose level. In patients with intolerable side effects or progression during MCT (either clinical or radiological), the protocol drugs would be stopped and further treatment would be according to the institutional protocols.

### Pretreatment Criteria

All patients will have to fulfil the following criteria prior to starting MCT. Each 4 weeks of treatment would be considered as one cycle.

Prior to first cycle:

1. Hemoglobin: > 10 g/dL
2. Total Leucocyte Count : > 3000 / cumm
3. Platelet Count : > 1,00,000 / cumm
4. AST / ALT : < 2.5 times upper normal limit of institutional value
5. Bilirubin: Total < 1.5 times upper normal limit of institutional value
6. Calculated serum creatinine clearance above 30 ml/min

**Prior to subsequent cycles:**

1. Hemoglobin: > 8 g/dL
2. Total Leucocyte Count : > 2000 / cumm
3. Platelet Count : > 80,000 / cum
4. AST / ALT : < 2.5 times upper normal limit of institutional value
5. Bilirubin: Total < 1.5 times upper normal limit of institutional value
6. Calculated serum creatinine clearance above 30 ml/min
7. Resolution of other toxicities to  $\leq$  Grade I.

## **11.2 Metronomic chemotherapy administration**

Chemotherapy will be administered with tablet erlotinib 150 mg ( fixed dose ) PO OD daily, capsule celecoxib 200 mg ( fixed dose ) PO BD daily and oral weekly methotrexate.

**In stage 1 : The dose of methotrexate will be according to the dose level**

**In stage 2 : The dose of methotrexate will be the dose selected from stage 1**

All chemotherapy medications will be taken 1 hour before breakfast. The methotrexate is available in 2.5 mg tablets. Hence the dose of methotrexate will be rounded off to the nearest lower numerical which is a multiple of 2.5. This could enable delivery of methotrexate without the need for breaking or crushing the tablets. All methotrexate tablets will be taken together.

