#### 4.8 PK-PD (Pharmacokinetics- Pharmacodynamics) study of Methotrexate

Pharmacokinetics of methotrexate is well described by two-compartment model. There are many publications describing PK-PD model for methotrexate. one study has described relationship between methotrexate concentration and homocysteine (HCY) levels. An indirect response model was used to describe the HCY concentrations. An  $E_{max}$  model was used to link the PK and PD model (Figure 3).

[figure not shown]

Figure 3. Scheme of the PK/PD model (CL=total body clearance; Q=intercompartmental clearance; V1=volume of the central compartment; V2=volume of the peripheral compartment; HCY=homocysteine;  $k_{in}$ =HCY formation rate constant;  $k_{out}$ =HCY elimination rate constant).

So far, no study is reported to describe PK-PD model for anti-angiogenic effect of methotrexate. Developing a model which describes relationship between methotrexate concentration and CESs and biomarkers like VEGF, sVEGFR-2 and sVEGFR-3 will be helpful to establish the OBD of methotrexate.

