## 6 Hypothesis

**Stage 1: Whether a lower dose of methotrexate is clinically and biologically more effective than 15 mg /m^2 weekly dose?** *The dose of methotrexate associated with maximum CBR at 2 months and/or decline in CEC at D7 of first cycle would be selected .*

**Stage 2 : Whether MCT-E combination of celecoxib, erlotinib and methotrexate (in OBD) would lead to a median PFS of > 3 months in platinum insensitive oral cancers?**

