### Delivery setting

The cycles may be delivered in inpatient and/or outpatient basis. Reported adverse events, potential risks and appropriate dose modifications are described in Section 13. No investigational or commercial agents or therapies other than those described below may be administered with the intent to treat the participant's malignancy.

The starting dose of methotrexate will be 15 mg/m^2. The dose of methotrexate in a given patient will remain fixed in the subsequent cycles subject to the dose modification criteria mentioned below. Dose de escalation will be done for methotrexate only as per the schedule mentioned below. Once the clinically effective and biologically optimal dose of methotrexate is discovered then this dose will be administered in subsequent stage 2 study.

| Dose Level                                                        | Dose of Methotrexate* |
|-------------------------------------------------------------------|-----------------------|
| Level 0 – Starting Dose                                           | 15 mg/m   |
| Intermediate dose level between dose level 0 & 1
(if required) | 13 mg/m   |
| Level 1                                                           | 12 mg/m   |
| Intermediate dose level between dose level 1 & 2 (if
required) | 10 mg/m   |

|                                                                |                      |
|----------------------------------------------------------------|----------------------|
| Level 2                                                        | 09 mg/m  |
| Intermediate dose level between dose level 2 & 3 (if required) | 07 mg/m  |
| Level 3                                                        | 06 mg/m  |
| Intermediate dose level between dose level 3 & 4 (if required) | 04 mg/m  |
| Level 4                                                        | 03 mg/m  |

Table 2: Dose levels of methotrexate for dose de escalation.

| Day | Agent               | Dose                                                                                               | Route                        | Schedule      |
|-----|---------------------|----------------------------------------------------------------------------------------------------|------------------------------|---------------|

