### 12.2 Laboratory interventions

#### Sample collection:

1. **Tumor tissues will be collected at baseline ( +1 month prior to 2 days post MCT start), C1D8 (+/- 2 days) and at progression.** Fresh(~20-30 mg) and formalin fixed tumor tissues will be used. Tumor content will be assayed and tissues having less than 60% of tumor will not be used for microarray analysis. Fresh tumor tissue will be subjected to extraction of DNA and total RNA while fixed tumor tissues will be used for IHC.
2. **20 ml of blood will be collected (5 ml in 3 EDTA tube and 5 ml in plain tube) at baseline collected at baseline ( +7 days prior to 1 days post MCT start) , C1D8(+/- 2 days) and at progression.** 1 EDTA tube each will be used for Flow cytometry, Microarray and ELISA. Fourth tube will be a reserve. 10 ml of blood will be used for separation of plasma (5 ml) and serum (5ml) which will be stored at -80°C, used for analysis of various parameters.
  - a. PK-PD Sample size collection restricted to stage 1
    - i. 5 ml blood will be collected at each time point. Immediately after collection, blood samples will be kept on ice till they are further process to separate plasma by centrifugation at 4°C. Plasma samples will be stored

at -80°C till further analysis of drug levels (Bioanalysis using LC-MS/MS) and levels of CECs and biomarkers.

| DRUG         | TIME POINTS FOR SAMPLING            | No. of Draws | Cycle and Day |
|--------------|-------------------------------------|--------------|---------------|
| Methotrexate | 0, 0.5, 1, 1.5 , 4, 6, 8, 24, 30 hr | 9            | C1D1,         |

3. **At the time of each monthly D30 (+/- 7 days) follow up 10 ml of blood will be collected in EDTA tube for the first 3 months for Flow cytometry and ELISA .**

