## **25 Feasibility**

On an average in TMC, 30 chemoresistant patients receive palliative chemotherapy for advanced oral cavity cancers per month. The maximum required sample size for the present study is 30 patients ( 6 x 5 dose levels). Assuming that only 10% of the eligible patients are willing to participate in this trial we expect 30 patients to be recruited within a period of 24 months from the date of start of recruitment. Hence around 70 patients ( cumulative number required for stage I/II ) would be recruited within 4 years.

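### Methotrexate is always rounded down to whole 2.5 mg tablets, so an optimal dose reported as 6 or 3 mg/m² would overstate the dose that patients took

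*Protocol*

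**What the plan says.** - **Tablets and rounding.** Section 11.2 states that "The methotrexate is available in 2.5 mg tablets" and that the dose is "rounded off to the nearest lower numerical which is a multiple of 2.5". The stated purpose is to give the drug "without the need for breaking or crushing the tablets". There is no exception for low levels.
- **Dose levels.** The table captioned "Table 2: Dose levels of methotrexate for dose de escalation" lists five main levels, 15, 12, 9, 6 and 3 mg/m² weekly, with optional intermediate levels between them. The dose column carries an asterisk, but no matching footnote appears in the text available to me.
- **Purpose of Stage 1.** Section 6 asks "Whether a lower dose of methotrexate is clinically and biologically more effective than" 15 mg/m² weekly. The level selected goes forward to Stage 2 under the same section 11.2.
- **Exposure data.** Section 12.2 provides nine methotrexate samples on day 1 of cycle 1, under the line "PK-PD Sample size collection restricted to stage 1". Section 4.8 expects that a model linking concentration to CECs and biomarkers "will be helpful to establish the OBD of methotrexate".
- **Size of a level.** Section 25 says "The maximum required sample size for the present study is 30 patients ( 6 x 5 dose levels").

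**The concern.** Stage 1 exists to produce one number, a dose in mg/m². Rounding down can only lower a dose or leave it unchanged, and the tablet is large relative to the lowest doses. If de-escalation ends at 6 or 3 mg/m², the reported optimal biological dose (OBD) would be higher than the dose that produced the CEC and disease-control results.

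The label also hides variation at 3 mg/m². Two patients whose BSA differs by 0.01 m² can take one tablet and two tablets under the same level.

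An example of the consequence, assuming a later user rounds to the nearest tablet (the protocol does not say this): two tablets are given at 3 mg/m² once BSA exceeds 3.75 / 3 = 1.25 m². Trial patients with BSA between 1.25 and 1.67 m² would have taken one.

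**Working it through.** **Inputs.** From the protocol: the 2.5 mg tablet, whole tablets only, rounding down (section 11.2), and the main levels of Table 2. BSA is not given. I assume cohort means of 1.50 to 1.80 m² with SD 0.10 or 0.15, and a uniform spread of 1.3 to 1.9 m². The protocol states no delivered-dose figure to reproduce.

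**Formulas.** Tablets = floor(level × BSA / 2.5). Delivered mg/m² = tablets × 2.5 / BSA. Delivered share = delivered / level.

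**Why the loss grows at low levels.** Rounding down loses about half a tablet on average, 1.25 mg. At BSA 1.6 that is 1.25 / 1.6 = 0.78 mg/m² at any level. As a share it is 5% of 15, 9% of 9, 13% of 6 and 26% of 3 mg/m². This is only a guide; at 3 mg/m² the exact figure depends strongly on BSA.

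**Cohort mean share of nominal (simulation):**

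| Assumed BSA (m²) | 15 | 12 | 9 | 6 | 3 |
|---|---|---|---|---|---|
| Mean 1.50, SD 0.10 | 94% | 93% | 91% | 84.7% | 58% |
| Mean 1.55, SD 0.15 | 95% | 93% | 91% | 85.8% | 65% |
| Mean 1.65, SD 0.15 | 95% | 94% | 91% | 87.0% | 72% |
| Mean 1.75, SD 0.15 | 95% | 94% | 92% | 88.5% | 81% |
| Mean 1.80, SD 0.10 | 95% | 94% | 92% | 90.6% | 88% |
| Uniform 1.3 to 1.9 | 95% | 93% | 91% | 88.2% | 71% |

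With SD 0.10, the 6 mg/m² figure is 84.7% at mean BSA 1.50 and 90.6% at 1.80, with a low of 83.9% at 1.55. Hence about 84 to 91%.

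**Single patients, BSA 1.4 to 1.8 m².** The share runs from 75 to 100% at 6 mg/m² and from 50 to 100% at 3 mg/m². At BSA 1.6 a patient takes 7.5 of 9.6 mg (78%) and 2.5 of 4.8 mg (52%). At BSA 1.7 it is 10 of 10.2 mg (98%) and 5 of 5.1 mg (98%).

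**The step at 3 mg/m².** Two tablets need 3 × BSA ≥ 5, so BSA ≥ 5 / 3 = 1.67 m². At 1.66 the patient takes 2.5 / 1.66 = 1.51 mg/m²; at 1.67, 5 / 1.67 = 2.99 mg/m². The cohort mean at this level is therefore not a typical patient's dose.

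**How often a group contains both tablet counts.** With p the share below 1.67 m², six patients include both with probability 1 − p⁶ − (1 − p)⁶:
- Mean 1.50, SD 0.10: p = 0.95, 25%.
- Mean 1.80, SD 0.10: p = 0.09, 44%.
- Mean 1.55, SD 0.15: p = 0.78, 77%.
- Mean 1.75, SD 0.15: p = 0.29, 87%.
- Uniform: p = 0.61, 94%.
- Mean 1.65, SD 0.15: p = 0.54, 97%.

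Six per level is the feasibility maximum in section 25, not a planned cohort size.

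**Do the main levels stay apart?** Delivered dose always exceeds level − 2.5 / BSA. At BSA 1.3 the maximum loss is 1.92 mg/m², less than the 3 mg/m² between main levels. For BSA 1.3 to 1.9 the delivered bands are 13.1–15.0, 10.3–12.0, 7.2–9.0, 4.5–6.0 and 1.5–3.0 mg/m². They do not overlap.

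**The case against.** The rule is stated openly in the same section as the dose table. The regimen is in effect the mg/m² level plus rounding down, and Stage 2 follows the same rule. The selected regimen is therefore repeated tablet for tablet, and the Stage 2 PFS estimate belongs to it. This stands. A reader might infer that Stage 2 would test a different dose from the one selected; the protocol does not support that.

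A reader might also infer that rounding scrambles the dose comparison or leads to the wrong level. It does not follow. The five main levels remain ordered and separate, and nothing shows that a decision would change. (An optional intermediate level can share a tablet count with the main level below it: at BSA 1.7, 4 and 3 mg/m² both give two tablets. I do not rest the point on that.)

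Pharmacokinetic sampling measures actual exposure in Stage 1 and may help to establish the OBD. That is a real safeguard for interpretation, but concentrations on one day do not correct the mg/m² label.

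The asterisk in Table 2 may lead to a footnote on rounding. I cannot exclude this; nothing in the available text settles it.

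Finally, deriving a delivered dose is ordinary analysis-plan work, and that plan is not shown. The point therefore rests on the stated combination of round-down rule and nominal label, not on a missing analysis. This objection lowers the priority.

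**Conclusion.** The point holds as a labelling problem that depends on where Stage 1 ends. At 9 mg/m² or above it is minor, with about 91 to 95% delivered on average. At 6 mg/m² the cohort mean is about 84 to 91% of nominal and at 3 mg/m² about 58 to 88%, for assumed mean BSA of 1.5 to 1.8 m² with SD 0.10. These are cohort means and must not be read as limits for single patients.

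The twofold step at BSA 1.67 m² follows from the protocol's own numbers and needs no distribution. How often a group mixes both tablet counts does need one: about 25 to 97% for six patients across the assumptions, so no single figure should be quoted.

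This is a cheap improvement, of low priority unless Level 3 or 4 is reached.

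**What to change.** Keep the dose levels, the rounding rule, the tablet strength and the adaptive model.

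1. For each Stage 1 patient, derive delivered mg/m² = tablets × 2.5 / BSA.
2. Report the OBD with its delivered mean and range and the rounding rule beside the nominal label. At 3 mg/m², also give the number of patients on one and on two tablets. A note to Table 2 would be enough in the protocol.
3. Add one sensitivity dose-response analysis by delivered dose. No patient moves between levels.

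The inputs are already needed to dispense the drug. The cost is one derived variable, one reporting line and one extra analysis. Allocation, sample size and Stage 2 dosing do not change. The downside is a reported OBD somewhat lower than its label, mainly at 3 to 6 mg/m².

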### Missing dose

In case the drugs are not taken prior to breakfast then they can be taken 2 hours after food. If the dose of erlotinib or celecoxib is missed at schedule time it can be taken within 12 hours on the schedule day. However the gap between doses taken on two consecutive days should be more than 12 hours. If the dose of erlotinib or celecoxib is missed on any day then it won't be compensated. If the patient cannot take for any reason the schedule medications ( erlotinib and celecoxib ) for more than 14 days then he would be withdrawn from the protocol.

In case of oral methotrexate as it would be given weekly if the the patient misses the schedule time of 1 hour before breakfast it can be taken at any time during the schedule day. If the scheduled day is miss it can be taken administered within next 2 days.

### Delivery setting

The cycles may be delivered in inpatient and/or outpatient basis. Reported adverse events, potential risks and appropriate dose modifications are described in Section 13. No investigational or commercial agents or therapies other than those described below may be administered with the intent to treat the participant's malignancy.

The starting dose of methotrexate will be 15 mg/m^2. The dose of methotrexate in a given patient will remain fixed in the subsequent cycles subject to the dose modification criteria mentioned below. Dose de escalation will be done for methotrexate only as per the schedule mentioned below. Once the clinically effective and biologically optimal dose of methotrexate is discovered then this dose will be administered in subsequent stage 2 study.

| Dose Level                                                        | Dose of Methotrexate* |
|-------------------------------------------------------------------|-----------------------|
| Level 0 – Starting Dose                                           | 15 mg/m   |
| Intermediate dose level between dose level 0 & 1
(if required) | 13 mg/m   |
| Level 1                                                           | 12 mg/m   |
| Intermediate dose level between dose level 1 & 2 (if
required) | 10 mg/m   |

|                                                                |                      |
|----------------------------------------------------------------|----------------------|
| Level 2                                                        | 09 mg/m  |
| Intermediate dose level between dose level 2 & 3 (if required) | 07 mg/m  |
| Level 3                                                        | 06 mg/m  |
| Intermediate dose level between dose level 3 & 4 (if required) | 04 mg/m  |
| Level 4                                                        | 03 mg/m  |

Table 2: Dose levels of methotrexate for dose de escalation.

| Day | Agent               | Dose                                                                                               | Route                        | Schedule      |
|-----|---------------------|----------------------------------------------------------------------------------------------------|------------------------------|---------------|
| D1  | Tablet Erlotinib    | 150 mg OD                                                                                          | PO 1 hour prior to breakfast | D1- D28       |
|     | Capsule Celecoxib   | 200 mg BD                                                                                          | PO 1 hour prior to breakfast | D1- D28       |
|     | Tablet Methotrexate | Stage 1 : Dependent of dose level , OD
Stage 2 : The dose of methotrexate selected from stage 1 | PO 1 hour prior to breakfast | D1,D8,D15,D22 |

Table 3: Chemotherapy schedule. Schedule will be repeated at 4 weekly intervals subject to resolution of toxicities and with dose modification mentioned below.

